##### *Anthropometry and body composition*

Height will be measured with a standardised wall mounted stadiometer to the nearest 0.1 cm. Body weight will be measured using digital scales to the nearest 0.1 kg. Total body lean mass, fat mass and percentage body fat will be determined from the total body DXA scan using a Hologic Discovery W dual-energy X-ray absorptiometry (DXA) machine with the APEX Software v3.2 (Hologic, Bedford, MA). All follow-up measurements will be analyzed using the ‘comparison’ feature of the Hologic APEX 3.2 analysis program. The short term co-efficient of variation for repeated measurements of total body lean mass and fat mass in our laboratory is 0.6% and 1.2%, respectively.

#### Other measures

##### *Biochemical and hormonal measures*

Participants will be directed to a local pathology collection centre following each testing visit to provide a fasted, morning (8 to 10 am) blood sample. Blood samples will be tested for serum calcium, albumin, phosphate, creatinine, alkaline phosphatase and C-reactive protein. Remaining serum will be aliquoted and stored at −80°C until completion of the study when samples will be analysed for the following hormonal measures: serum 25-hydroxyvitamin D, parathyroid hormone (PTH) and insulin-like growth factor-1 (IGF-1).

##### *Lifestyle and medical history*

All participants will complete a lifestyle questionnaire detailing education background, current and past employment, history of disease(s)/illnesses, previous fractures, family history of fractures/osteoporosis, current medications and dietary supplements, average weekly alcohol consumption, and weekly television viewing and sitting time. For female participants, menstrual history will be documented including age of onset of menopause, menstrual cycle regularity and history of oral contraceptive and HRT use.

##### *Compliance*

Compliance with the *Osteo-cise* exercise program will be evaluated via self-completed exercise cards that research staff will collect from each health and fitness centre approximately 3-monthly throughout the intervention. Compliance with taking the prescribed calcium and vitamin D supplements will be determined by a medication count when remaining bottles are returned at each testing appointment.

##### *Habitual physical activity*

The CHAMPS physical activity questionnaire will be used to assess current participation in a range of low, moderate, and vigorous physical activities at baseline, 6, 12 and 18 months of the study. This self-report questionnaire has been designed for use in older adults and has been found to be reliable, valid and sensitive to changes in physical activity behaviour [55]. Participants will document their weekly frequency and duration of participation in a ‘typical week’ of the preceding four weeks. The results will be reported as estimated kilojoules per week spent in moderate to high intensity activities. The total number of hours spent performing weight-bearing impact activities will also be determined from this questionnaire.

##### *Diet*

Nutrient intakes will be assessed at each testing visit using 24-hour dietary recall whereby participants will record the type, amount and time of consumption of all food and fluid consumed over a 24-hour period. Participants will be encouraged to provide as much detail as possible including brand names of known foods and exact cooking methods. This questionnaire will be checked for completeness by research staff at each respective testing appointment so that any ambiguous or missing information can be clarified. Dietary information from the questionnaires will be entered and analysed using Australia-specific dietary analysis software (Foodworks, Xyris Software, Highgate Hill, Australia).

##### *Cost Utility Analysis (CUA)*

The CUA will determine the quality of health outcomes averted by the *Osteo-cise: Strong Bones for Life* program. The outcome will be expressed as a cost per quality-adjusted life-years (QALYs) gained. This method of cost analysis involves an assessment of incremental change in health-related quality of life and the monetary costs related to the development and implementation of the *Osteo-cise* program as well as monetary costs related to any adverse events such as injury. The change in quality of life between the groups will be calculated using the difference in QALYs from baseline to the 12-month time point and will be determined using the EuroQoL-5D questionnaire [56].

The EuroQoL-5D considers five dimensions of health, including mobility, self-care, usual activities, pain/discomfort and anxiety/depression. The responses will be scored/weighted using recently published algorithms for Australia [57]. The assessment of monetary costs will include an incremental cost related to program development plus the costs of implementing the program including staff time and costs of all materials/equipment. Costs related to injury or adverse events will also be included (medical care, non-medical care and indirect costs). The Australian Medicare Scheduled fees will be used as uniform unit costs where applicable.

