### Sample size

In order to calculate the number of participants required for this study, power calculations were performed based on BMD and functional muscle power results from previous exercise intervention trials [37,39]. It was estimated that 60 participants in each group would provide at least 90% power to detect a 1.8% difference (assuming a standard deviation [SD] of 3.5) for the change in femoral neck BMD at p < 0.05 (two-tailed). For functional muscle power, we estimated that 24 participants would provide 90% power to detect a 15% difference for the change between the groups (two-tailed, P < 0.05) assuming a SD of 15%. Therefore with an anticipated 20% dropout rate, a minimum of 72 participants per group will be required (144 in total).

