### Statistical analyses

Statistical analyses will be computed using STATA statistical software (version 11.0, Stata Corp, College Station, TX). Baseline and demographic data will be presented using descriptive statistics. All intervention data will be analysed according to the principle of intention-to-treat (ITT) and adjusted for multiple comparisons where appropriate. Non- normally distributed data will be transformed prior to analysis. Comparisons between the groups for all continuous primary and secondary outcomes variables will be made using repeated measures analysis of variance (ANOVA) for both time and group-by-time interactions. ANOVA or analysis of covariance (ANCOVA) will be used for absolute and/or percent changes after 12 and 18 months after adjusting for relevant confounders. Falls will be analysed according to the rate of falls per person-year, the proportion sustaining one or more falls and injurious falls during follow-up. The number of falls will be analysed using Poisson regression models with robust standard errors to allow for non-independence of multiple events for the same participant and negative binomial regression models allowing for overdispersion.

Cost utility analysis: Cost data is often skewed and thus not normally distributed. Therefore the Kruskal-Wallis one-way analysis of variance will be used to test the difference in cost and quality of life between the ‘usual care’ and exercise groups. To investigate the difference in cost between the groups, the transformed cost variable will be used as the dependent variable in a multivariable ordinary least square (OLS) regression model. All data will be presented as means ± SD or 95% CI unless stated. The significance level will be *p* < 0.05 or smaller where adjusted for multiple comparisons.

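### The QALY gain is defined ambiguously, and no baseline-adjusted estimator is named for it, although EQ-5D is collected at 0, 6 and 12 months

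*Protocol article*

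**What the plan says.** The section Cost Utility Analysis (CUA) sets the result: "The outcome will be expressed as a cost per quality-adjusted life-years (QALYs) gained". It describes the effect side as "an assessment of incremental change in health-related quality of life" and then gives the calculation: "The change in quality of life between the groups will be calculated using the difference in QALYs from baseline to the 12-month time point". The utilities come from the EQ-5D, which Table 3 schedules at baseline, 6, 12 and 18 months.

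The cost-utility paragraph under Statistical analyses says that "the Kruskal-Wallis one-way analysis of variance will be used to test the difference in cost and quality of life" between the groups. It adds that "the transformed cost variable will be used as the dependent variable in a multivariable ordinary least square (OLS) regression model". No regression is named for QALYs. Earlier in the same section, a general sentence offers ANOVA or ANCOVA for "absolute and/or percent changes after 12 and 18 months after adjusting for relevant confounders". It mentions neither QALYs nor baseline EQ-5D.

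**The concern.** A QALY is utility accumulated over time, so it has no value at baseline from which a change could be taken. The sentence therefore has to be interpreted, and the two interpretations give different numbers from the same data.

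- **Change score:** month-12 utility minus baseline utility. This credits the gain seen at month 12 as if it had been held all year, and it does not use the month-6 value.
- **Accrued QALYs:** the area under the utility curve from 0 to 12 months. This is the usual meaning, but baseline utility is part of that area and also predicts the later values. An unadjusted comparison therefore carries any chance baseline gap into the result.

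The named test settles neither question. Kruskal-Wallis takes no covariates and gives no mean difference, and a cost per QALY needs a mean difference in its denominator. If the true gain is small, a modest change in that denominator moves the ratio a good deal.

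**Working it through.** The article states no QALY, EQ-5D or cost figure, so there is none to reproduce.

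**Inputs from the article:** EQ-5D at 0, 6 and 12 months (Table 3); 72 randomised per group, or 60 before the dropout allowance (Sample size).

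**Assumed inputs, not in the article:** utility SD 0.12-0.20 at every visit; correlation ρ between any two visits 0.5-0.7; a month-6 effect between zero and the full month-12 effect.

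**1. Area under the curve.** By the trapezoid rule, in years: QALY = 0.25·u0 + 0.5·u6 + 0.25·u12.

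**2. Change score against area, no baseline gap.** Let d6 and d12 be the arm differences in utility at months 6 and 12. The area is 0.5·d6 + 0.25·d12 and the change score is d12, so their ratio is 1/(0.5·d6/d12 + 0.25).

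| d6/d12 | Area per unit of d12 | Change score ÷ area |
|---|---|---|
| 0 (all after month 6) | 0.25 | 4.0 |
| 0.25 | 0.375 | 2.67 |
| 0.5 (linear) | 0.50 | 2.0 |
| 0.75 | 0.625 | 1.6 |
| 1 (complete by month 6) | 0.75 | 1.33 |

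For an illustrative month-12 gain of 0.04, the areas are 0.010 (d6/d12 = 0), 0.020 (linear) and 0.030 (complete by month 6). Under the accrued reading the factor is 1.0.

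**3. Chance baseline gap, accrued QALYs unadjusted, 72 per arm.**
- SE of the gap = SD·√(2/72): 0.12 × 0.1667 = 0.020 and 0.20 × 0.1667 = 0.033.
- Mean absolute gap = 0.798 × SE: 0.016 and 0.027.
- Share passing into the QALY difference = 0.25 + 0.75ρ: 0.625 at ρ = 0.5 and 0.775 at ρ = 0.7.
- Typical shift: 0.016 × 0.625 = 0.010 and 0.0266 × 0.775 = 0.021 QALY.
- With 60 per arm, multiply by √(72/60) = 1.095: about 0.011 to 0.023.

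**4. Gain from adjustment.** In units of SD², the variance of the area is 0.375 + 0.625ρ and its covariance with baseline is 0.25 + 0.75ρ. The share of variance explained by baseline is (0.25 + 0.75ρ)²/(0.375 + 0.625ρ):
- ρ = 0.5: 0.3906/0.6875 = 57%
- ρ = 0.6: 0.4900/0.7500 = 65%
- ρ = 0.7: 0.6006/0.8125 = 74%

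The SE of the arm difference is SD·√(0.375 + 0.625ρ)·√(2/72), multiplied after adjustment by √(1 − share). At SD 0.12 and ρ = 0.5 it falls from 0.0166 to 0.0109. At SD 0.20 and ρ = 0.7 it falls from 0.0300 to 0.0153.

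**5. Baseline gap under the change score.** The gap is already subtracted. What is left is −(1 − ρ) per unit of gap, that is −0.5 to −0.3, against +0.625 to +0.775 for the unadjusted area. It is smaller here and of opposite sign.

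**The case against.** The quantity being differenced is called QALYs, and QALYs are by definition accrued. The natural reading is then the between-group difference in QALYs over the first year, with no inflation at all. Nothing in the article says that month 6 is dropped. Under randomisation an unadjusted difference is unbiased; a chance baseline gap is part of its sampling error, and a confidence interval would reflect it. The trapezoid rule and a covariate list are details that an article commonly leaves to a full plan. The general ANCOVA sentence leaves room for adjustment, and Table 3 places EQ-5D among the secondary measures, for which repeated-measures ANOVA is planned. Every SD, correlation and effect size used above is assumed.

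Most of this stands, and it rules out stronger conclusions that a reader might draw:
- That the cost per QALY will be wrong by a factor of two. This needs both the change-score reading and a linear rise.
- That inflation and baseline carry-over act together. They belong mainly to different readings.
- That baseline adjustment is excluded. It is only not named for QALYs.
- That a chance baseline gap makes the result biased. It costs precision.

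What the objection does not remove is that the article does more than stay silent. It commits to a loosely worded contrast and to a rank test that can neither adjust for baseline nor supply the mean difference that the ratio needs. The general ANCOVA sentence concerns changes at 12 and 18 months, and the cost-utility paragraph then sets its own methods.

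**Conclusion.** The point holds as an ambiguity together with an avoidable loss of precision, not as a demonstrated error. The definition allows two quantities. If the change score were taken as the QALY gain, that gain would be overstated, and the cost per QALY understated, by a factor of 1.33 to 4.0, for a month-6 effect between zero and the month-12 effect. If accrued QALYs are compared without adjustment, the estimate is unbiased but less precise than the collected data allow. The typical chance shift is 0.010-0.021 QALY with 72 per arm, and adjustment would remove 57-74% of the QALY variance. These last figures rest on the assumed SD of 0.12-0.20 and equal between-visit correlations of 0.5-0.7.

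The BMD and stair-climb primary outcomes are untouched. The change is worth making because it is a better method than the one stated under either reading.

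**What to change.** In Cost Utility Analysis (CUA), state that QALYs are the area under each participant's EQ-5D utility curve from baseline to 12 months, by the trapezoid rule using the baseline, 6-month and 12-month values.

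In the cost-utility paragraph of Statistical analyses, state that the incremental QALY used in the cost per QALY is the between-arm mean difference, with its confidence interval, from a regression of QALYs on arm and baseline EQ-5D utility. This can replace the Kruskal-Wallis test for quality of life or stand beside it.

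The cost is wording only: all the EQ-5D values are already scheduled. If a change score had been intended, the reported QALY gain will probably be smaller and the cost per QALY higher.

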##### *Osteoporosis health beliefs and knowledge*

To evaluate the effect of the program on each participant’s knowledge and health beliefs related to osteoporosis, the Osteoporosis Knowledge Assessment Tool (OKAT) [58] and Osteoporosis Health Belief Scale (OHBS) [59] will be used. The OKT is a 20-item instrument with ‘true’, ‘false’ and ‘don’t know’ response options for measuring osteoporosis knowledge, and has good psychometric properties in Australian adults [58]. Participants are scored on their percentage of correctly answered items. The OHBS questionnaire will measure each participant’s health beliefs related to osteoporosis, exercise behaviours and calcium intake. Participants will rate each of the 42 items on a 5-point scale (1-strongly disagree, 2-disagree, 3-neutral, 4-agree and 5-strongly agree). The OHBS has seven subscales including Seriousness, Health Motivation, Calcium Benefits, Calcium Barriers, Exercise Benefits and Exercise Barriers. The test-retest reliability is 0.90, and 0.71 to 0.82 for the individual subscales of this test [59].

##### *Health-related Quality of Life*

Health-related quality of life will be assessed at each visit using the SF-36 questionnaire, which is a general measure of health status including eight scales: Physical functioning, Role-Physical, Bodily pain, General Health, Vitality, Social Functioning, Role-Emotional and Mental Health [60]. This test yields a score from 0 to 100, where 0 represents the lowest and 100 represents the highest quality of life. Reliability scores of above 0.80 and empirical validity of 0.80 to 0.90 have been reported in the literature for both the physical and mental health measures [60].

### Statistical analyses

Statistical analyses will be computed using STATA statistical software (version 11.0, Stata Corp, College Station, TX). Baseline and demographic data will be presented using descriptive statistics. All intervention data will be analysed according to the principle of intention-to-treat (ITT) and adjusted for multiple comparisons where appropriate. Non- normally distributed data will be transformed prior to analysis. Comparisons between the groups for all continuous primary and secondary outcomes variables will be made using repeated measures analysis of variance (ANOVA) for both time and group-by-time interactions. ANOVA or analysis of covariance (ANCOVA) will be used for absolute and/or percent changes after 12 and 18 months after adjusting for relevant confounders. Falls will be analysed according to the rate of falls per person-year, the proportion sustaining one or more falls and injurious falls during follow-up. The number of falls will be analysed using Poisson regression models with robust standard errors to allow for non-independence of multiple events for the same participant and negative binomial regression models allowing for overdispersion.

Cost utility analysis: Cost data is often skewed and thus not normally distributed. Therefore the Kruskal-Wallis one-way analysis of variance will be used to test the difference in cost and quality of life between the ‘usual care’ and exercise groups. To investigate the difference in cost between the groups, the transformed cost variable will be used as the dependent variable in a multivariable ordinary least square (OLS) regression model. All data will be presented as means ± SD or 95% CI unless stated. The significance level will be *p* < 0.05 or smaller where adjusted for multiple comparisons.

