#### Randomisation

Following baseline testing participants will be randomised into either the *Osteo-cise: Strong Bones for Life* program or a self-management control group, stratified by sex, by an independent staff member not involved in the study using a computer generated random numbers table (Microsoft Excel). To avoid any potential contamination any couples enrolled in the study will be randomised into the same group. A flow diagram of the study protocol is outlined in Figure 1.

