#### Primary outcomes

The primary outcome measures will be changes in proximal femur and lumbar spine BMD and lower limb functional muscle power.

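### The protocol names no lead analysis for the continuous primary outcomes and does not fix adjustment for baseline or sex; one pre-specified ANCOVA would be a free improvement

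*Protocol article*

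**What the plan says.** The Statistical analyses section describes two between-group analyses of the continuous primary and secondary outcomes.

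- Comparisons "will be made using repeated measures analysis of variance (ANOVA) for both time and group-by-time interactions". No covariate is named.
- "ANOVA or analysis of covariance (ANCOVA) will be used for absolute and/or percent changes after 12 and 18 months after adjusting for relevant confounders". The confounders are not listed, and no rule selects the model or the scale.

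Nothing says which of the two leads.

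Other sections do not settle it:

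- Under Primary outcomes, "The primary outcome measures will be changes in proximal femur and lumbar spine BMD and lower limb functional muscle power". This gives no scale for the change.
- The Sample size section works in percent differences, but the analysis section is not tied to that scale.
- The Randomisation section says that allocation is "stratified by sex, by an independent staff member not involved in the study". Sex is the only stratification factor named, and it appears in no described model.

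**The concern.** Three things are left open for the outcomes that decide the trial: the model, the scale of change, and the covariates.

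The wording is also unclear within itself. A one-way ANOVA of change adjusts for nothing. An ANOVA with further factors could take in sex, but not a continuous baseline value.

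Two consequences follow. First, an unadjusted comparison of changes is permitted. It lets chance baseline imbalance into the estimate and is less precise than an analysis that conditions on baseline. Second, several versions of the same comparison fit the text, so a reader of the results could not tell whether the reported one was chosen in advance.

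The reference to confounders does not help. Randomisation removes systematic baseline confounding, so the reasons to adjust are precision and agreement with the stratified design. The term does not limit covariates to baseline variables either, and Table 3 has activity, diet and serum 25-hydroxyvitamin D measured at follow-up as well as at baseline.

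**Working it through.** **1. The plan's own figures, as a reference point.** For femoral neck BMD, tested two-sided at the 5% level, the Sample size section states: "60 participants in each group would provide at least 90% power to detect a 1.8% difference (assuming a standard deviation [SD] of 3.5". With 60 per group, SE = 3.5 × √(2/60) = 0.639 and 1.8/0.639 = 2.817. Power is Φ(2.817 − 1.960) = 80.4%. The stated 90% is not reproduced; that is a separate matter, and 80.4% serves below only as the unadjusted reference. For stair-climb power, "24 participants would provide 90% power to detect a 15% difference for the change between the groups", with an SD of 15%. Read as 24 per group, power is 93.4%, so the statement holds on that reading.

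**2. Precision of ANCOVA against a change score.** Let σ² be the outcome variance, assumed equal at baseline and follow-up, and r the baseline to follow-up correlation.

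- Change score: 2σ²(1 − r)
- ANCOVA residual: σ²(1 − r²)
- Ratio: (1 − r²) / [2(1 − r)] = (1 + r)/2

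The protocol gives no correlation, so r is shown over a range.

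| r (assumed) | Variance ratio | Reduction in SE, 1 − √ratio |
|---|---|---|
| 0.70 | 0.85 | 7.8% |
| 0.80 | 0.90 | 5.1% |
| 0.90 | 0.95 | 2.5% |
| 0.95 | 0.975 | 1.3% |

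Values of 0.7 to 0.8 are taken as plausible for stair-climb power, and 0.95 for BMD.

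**3. What this does to power.**

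- BMD, ratio 0.975: SD becomes 3.5 × √0.975 = 3.456, SE = 0.631 and 1.8/0.631 = 2.853. Power is Φ(0.893) = 81.4%, against 80.4% unadjusted.
- Reaching 90% at 60 per group would need covariates that explain about 24.5% of the variance of change. By baseline alone this means (1 + r)/2 = 0.755, so r of about 0.51. Nothing in the protocol supports that.
- Stair-climb power with 60 per group: 15/(15 × √(2/60)) = 5.48 and Φ(5.48 − 1.96) exceeds 99.9%. Here the gain is a narrower interval, not power.

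**4. The repeated measures ANOVA does not replace this.** It treats baseline as one of the time points. Its group contrast between a visit and baseline is the difference in mean change, so it is a change-score comparison, and no sex term is named.

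**5. Room for choice.** ANOVA or ANCOVA, times absolute or percent, gives 2 × 2 = 4 versions at each time point. A null simulation shows the possible size. It used 60 per arm and 3,000 runs per setting. The assumptions were baseline CV 0.15 with SD of change 3.5% (BMD-like) or CV 0.30 with SD 15% (stair-power-like), and a baseline to change correlation of −0.1 to −0.5. The ANCOVA used baseline and sex. Taking the smallest of the four p-values at 12 months gave a type I error of 6.5% to 9.9% per outcome instead of 5%. Monte Carlo error is about half a percentage point. This is a worst case: it supposes that the most favourable version is always reported.

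**The case against.** A condensed article commonly leaves the covariate list to the SAP, and an SAP may exist. The unnamed confounders may well include baseline and sex. The repeated measures ANOVA comes first in the text, so the second sentence can be read as supporting it. Outcomes are analysed as changes, which already remove each participant's own level, including any difference in level between the sexes. Measurement error is small: the protocol reports CVs of 0.8% to 1.5% for BMD and 2.2% for the stair climb. Percent change is the scale on which the trial was sized. The section also promises adjustment for multiple comparisons.

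Much of this stands. A missing covariate list alone would be no finding, and the precision gain for BMD is small. The harm from leaving out sex cannot be sized, because nothing shows that sex predicts change. Omitting a stratification factor usually makes standard errors conservative, so the cost would be precision and not false positives.

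Three things remain. The text does not merely leave detail out: it offers alternatives for the primary outcomes and permits an unadjusted one. Reading the repeated measures ANOVA as the lead is an inference that the text does not state. The multiplicity promise names no method and does not address a choice between models or scales.

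**Conclusion.** The point holds as a free improvement, not as an error that invalidates the trial. No lead analysis is named, adjustment for baseline and sex is not fixed, and a less precise analysis is permitted when a better one needs no new data. The variance reduction is 10% to 15% for stair-climb power and about 2.5% for BMD. These figures rest on assumed correlations and equal variances.

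A reader might infer more than the protocol supports:

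- *That baseline and sex are excluded.* They are unnamed, not ruled out.
- *That eight analyses compete per outcome.* Both 12 and 18 months are planned, so time point is not one of the alternatives. The menu is at most four at each. Choosing the better visit as well would raise the simulated error to about 10% to 15%, but the text does not offer that choice.
- *That the plan adjusts for mediators.* The wording permits follow-up covariates but does not propose them. Activity, diet and vitamin D are also measured at baseline. Exercise cards exist only for the intervention programme, so exercise adherence could not serve as a covariate in a between-group model.
- *That adjustment would repair the power calculation.* At r = 0.95 it adds about one percentage point.

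**What to change.** State one lead model for each continuous outcome: the follow-up value at 12 and at 18 months regressed on group, the baseline value of that outcome, and sex. Using the change in place of the follow-up value gives the same group effect once baseline is in the model.

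Choose one scale in advance. If a percent effect is wanted, to match the basis of the sample size, model the log outcome with log baseline and back-transform the group difference.

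Replace the reference to confounders with a short rule: further covariates are pre-specified baseline variables, used in sensitivity analyses only, and no post-randomisation variable enters a between-group model. If the repeated measures ANOVA is kept, label it as supporting.

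The cost is a sentence or two. Sex is known at randomisation and Table 3 already collects the baseline values, so no visit, measurement or change in sample size is needed.

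### The planned tests of cost and quality of life, and the transformed-cost regression, do not target the mean differences on which a cost per QALY rests

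*Protocol article*

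**What the plan says.** The section Cost Utility Analysis (CUA) defines the result: "The outcome will be expressed as a cost per quality-adjusted life-years (QALYs) gained". The effect component is the between-group change in quality of life, "calculated using the difference in QALYs from baseline to the 12-month time point", scored from the EuroQol-5D. On the cost side, "The assessment of monetary costs will include an incremental cost related to program development plus the costs of implementing the program", with injury and adverse-event costs added.

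The Statistical analyses section gives its reason for the method, "Cost data is often skewed and thus not normally distributed", and draws two consequences. First, "the Kruskal-Wallis one-way analysis of variance will be used to test the difference in cost and quality of life" between the groups. Second, for the difference in cost, "the transformed cost variable will be used as the dependent variable in a multivariable ordinary least square (OLS) regression model". It does not name the transformation or state any retransformation. The only reference to means is a general reporting rule: "All data will be presented as means ± SD or 95% CI unless stated".

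**The concern.** A cost per QALY is the difference in mean cost divided by the difference in mean QALYs. Arithmetic means are needed because a payer's total bill is the mean cost times the number of people treated. Medians, ranks and transformed-scale averages do not have that property.

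With two groups, Kruskal-Wallis is the Wilcoxon rank-sum test, which asks whether one group's values tend to exceed the other's. Least squares on a transformed cost estimates a difference on the transformed scale. Neither estimates the numerator of the ratio, and the rank test does not estimate the denominator. Skewness is a reason to be careful about inference on means, not a reason to change the quantity being compared.

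At stake is an economic report whose p-values and adjusted cost estimate may disagree with the mean costs that enter its own ratio. This trial is prone to that, because one arm carries a program cost for everyone while injury costs arise in only some participants of either arm.

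**Working it through.** The article gives no cost, QALY or variance figures, so there is no stated result to reproduce. The check sets the outcome against the methods and then illustrates the gap. All cost inputs below are assumptions.

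**Outcome against method**
- Numerator: difference in mean cost. Stated methods: a rank test, and a regression on transformed cost.
- Denominator: difference in mean QALYs. Method stated in the cost-utility paragraph: a rank test only.

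**Illustration 1: equal true mean costs, program cost in one arm only**

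Inputs: 60 per arm (the evaluable number in Sample size); program cost 1 for each intervention participant and 0 for controls; a small shared cost of 0.1 in both arms; lognormal injury costs (log-SD 0.8 to 1.2) in a proportion p_I of intervention and p_C of control participants; two-sided 0.05. The regression is run on log cost, as one possible transformation.

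For equal means, 1 + p_I × m = p_C × m, so the mean injury cost is m = 1/(p_C − p_I):
- 10% v 30%: 1/0.20 = 5
- 15% v 30%: 1/0.15 = 6.7
- 20% v 40% and 30% v 50%: 1/0.20 = 5
- 30% v 60%: 1/0.30 = 3.3

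Rejection rates, where the true mean difference is zero:

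| Injured, intervention v control | Kruskal-Wallis | OLS on log cost | Welch test of means |
|---|---|---|---|
| 10-15% v 30% | 99-100% | about 100% | 5-8% |
| 20% v 40% | 88-98% | about 100% | 4-5% |
| 30% v 50% | a little under 60% up to 90% | 97-99% | about 5% |
| 30% v 60%, log-SD 0.8 | about 32% | about 94% | about 5% |

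**Illustration 2: lognormal costs with unequal spread, 60 per arm, 4000 runs**

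For a lognormal cost, mean = median × exp(s²/2), where s is the log-SD.
- Equal means of 1000, s = 1.2 v 0.6. The factors are exp(0.72) = 2.054 and exp(0.18) = 1.197, so the medians are 1000/2.054 = 487 and 1000/1.197 = 835. The geometric mean ratio is exp(0.72 − 0.18) = 1.72 although the mean difference is zero. Rejection: Kruskal-Wallis 85%, log-OLS 88%, Welch 10%.
- Equal means, s = 1.0 v 0.8 (milder). Rejection: 18%, 18% and 4%.
- Equal medians of 1000, s = 1.2 v 0.6. The means are 2054 and 1197, a true difference of 857 per person. Rejection: Kruskal-Wallis 6%, log-OLS 5%, Welch 51%.
- Equal medians, s = 1.0 v 0.8. The means are 1649 and 1377, a difference of 272. Rejection: 5%, 5% and 10%.

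The planned methods can therefore depart from the mean cost difference in either direction. No simulation was done for QALYs; for the denominator the argument is only that a rank test does not estimate a mean difference.

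**The case against.** The best defence is that the plan does not derive the ratio from ranks or transformed coefficients. The CUA section says a QALY difference will be calculated, and the general reporting rule allows mean costs with intervals to be shown, so a point ratio can be formed. EQ-5D is also listed among the secondary measures in Table 3, and continuous secondary outcomes are elsewhere assigned ANOVA or ANCOVA. Retransformation, for example by smearing, could bring the cost model back to means. This stands as far as the point estimate goes. It does not rescue the named tests or the adjusted cost model, which are stated choices and not gaps left to a fuller plan.

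Stronger readings are tempting but are not supported:
- A reader might infer that the rank test will be significant whatever the mean costs are. Illustration 1 falls to about 32%, and the rates above 99% need an average injury cost 5 to 6.7 times the whole program cost. If injury costs were equal in both arms, rejection would be correct, because the means would then truly differ by the program cost.
- A reader might infer that the model compares geometric means, or that a log fails for near-zero control costs. The transformation is not named, and a log is undefined at zero, not at small positive values. The article does not say whether the free supplements given to both arms are costed.
- A reader might infer that the ratio will have no interval and that QALYs will go unadjusted for baseline utility. The article is silent on both, and a condensed article commonly leaves them to the full protocol or analysis plan.

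**Conclusion.** The point holds in this limited form: the stated inference on cost and quality of life, and the stated adjusted cost estimate, do not target the components of the cost per QALY that the article itself sets as the outcome. This follows from the text and needs no assumed figure.

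The practical size is uncertain. With equal mean costs, false signals of a cost difference ranged from about 32% to over 99% for Kruskal-Wallis and from 94% to 100% for least squares on log cost, against about 4% to 8% for a test of means. These figures rest on 60 per arm, assumed injury proportions, lognormal injury costs averaging 3.3 to 6.7 times the program cost, and a log transformation. With equal medians and unequal spread, the same methods missed a mean difference of 857 in about 94% to 95% of runs (100 − 6 and 100 − 5).

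This is a health-economic analysis; the primary bone density and stair-climb outcomes are unaffected. The paragraph should be corrected before the economic analysis is run.

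**What to change.** Replace the Kruskal-Wallis test and the transformed-cost regression, as the basis for inference, with:
- the difference in arithmetic mean cost, by least squares or a generalised linear model on untransformed cost;
- the difference in mean QALYs, adjusted for the baseline EQ-5D already collected;
- intervals for both, and for the cost per QALY or net benefit, by non-parametric bootstrap of each participant's cost-QALY pair. Couples should be resampled together, because the Randomisation section allocates them to the same group.

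The cost is a rewrite of one paragraph and slightly more analysis work, with no extra data. The price is less precision: comparisons of mean cost are noisier when costs are highly skewed. In Illustration 2 the test of means found the difference of 857 in only 51% of runs, and its false-positive rate reached 10% under the most unequal spread. The intervals should therefore be expected to be wide.
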